Despite these data, the use of TAI remains a matter of debate. In addition, there are only few randomized clinical trials so far comparing TAI with best supportive care (8, 9, 11, 12). Main limitations of this study are that a significant amount of patients (six patients, reduction of 27.27%) dropped out of the intervention (TAI) group (9), the small numbers, and the short follow-up period (8, 11, 12).

Thus far, there are no randomized clinical trials confirming or denying the hypothesis regarding the most effective treatment for LARS. Treatment recommendations for LARS have been published in 2021 (13). Here, authors propose to initiate the treatment with best supportive treatment. If it fails, transanal irrigations are started. Moreover, if this fails, invasive procedures are recommended (such as sacral nerve modulation or stoma). Some authors recommend the perineal stoma as an alternative stoma formation site in patients were sphincter preservation is not possible (14). However, data on the risk of LARS in this subgroup of patients is still lacking.

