### Randomization

Individuals participating in this study will be randomly divided into groups A and B by randomization (computer-generated random numbers and sealed envelopes will be used). The probability of falling into one or the other group is equal.
•Group A. This is a group of patients who will be subjected to transanal irrigation (experimental).•Group B. This is a group of patients who will receive only the best currently in use maintenance treatment (control).During the research, the name and surname of the subject will be replaced by a special code, restricting the identity of the subject. This code will be used in all study documents except the consent form. Only the main researcher and his representatives will have access to these data, and the staff performing the statistical analysis will not know which group the subject belongs to. Only the data analysts will be blinded to the patients groups (will get only data with names of Groups A and B, without any notification, of which group is which).

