### Assessments

Data collection will take place during the patient visit. Demographic and clinical examination data will be collected from the medical documentation at the research center. During the visit, the patient's complaints after the operation (defecation, deterioration of quality of life) will be recorded, and LARS, Wexner scale, and quality of life questionnaires will be filled during the visit. Questionnaires and scales will be filled again during the visit every 3 months for 1 year. Other tests that will be performed during the visit will be long-term follow-up tests, an integral part of the treatment, not related to the clinical trial.

At the second stage, a longer follow-up will be planned—for more than 2 years after the end of treatment.

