### Sample size

A sample size of 40 is planned (an improvement of 5 points on the LARS scale):
•20 transanal irrigation group (experimental) and•20 best supportive care group (control).To demonstrate a 5-point difference (with 80% certainty) between the intervention group and the control group, 34 patients were required to participate in the study (17 in each study arm). Taking into account a drop off of 20%, at least 20 patients per group will be needed. The primary endpoint was LARS score analyzed by unpaired *t* test.

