### Statistical analysis

For statistical analysis, we will use the intention to treat principle.

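### The primary unpaired t test makes no efficient use of the baseline LARS score and no stated use of the repeated scores; a baseline-adjusted comparison would gain power at almost no cost

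*Protocol article*

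**What the plan says.** The Sample size section fixes the primary test: "The primary endpoint was LARS score analyzed by unpaired" *t* test. It names no visit and no covariate, and does not say whether the value tested is the score at follow-up or its change from baseline. The planning statement is "To demonstrate a 5-point difference (with 80% certainty) between the intervention group and the control group, 34 patients were required", that is 17 per arm, followed by "Taking into account a drop off of 20%, at least 20 patients per group will be needed". No SD and no alpha are given.

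Other sections bear on what the test could have used:

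- **Eligibility criteria:** entry requires a LARS score above 30, so every patient has a baseline score.
- **Assessments:** "Questionnaires and scales will be filled again during the visit every 3 months for 1 year". This schedules follow-up scores at 3, 6, 9 and 12 months.
- **Objectives** and **Outcome measures:** results are described as a decrease or change in the absolute score, and as the proportion of patients who achieve it.
- **Statistical analysis:** "we will use the intention to treat principle". The article gives no missing-data method.

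**The concern.** A two-sample t test reduces each patient to a single number and compares two means. Here up to five LARS scores per patient are planned, one at baseline and four afterwards. In a trial of 40 patients, the part of the outcome that baseline can predict is worth removing from the error term, and the trial already collects what is needed to do so.

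The wording leaves two readings, and neither uses the baseline well. If the raw follow-up score is tested, the baseline plays no part. If the change score is tested, the baseline is subtracted with a fixed weight of one, which adds noise when the correlation between baseline and follow-up is modest. What is at stake is power, and the width of the confidence interval, in a trial planned at 80% with little room for loss.

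**Working it through.** **Inputs.** From the Sample size section: difference 5 points, power 80%, 17 per arm. From Randomization: equal allocation ("The probability of falling into one or the other group is equal"). Not in the article, hence assumed: two-sided alpha 0.05, and a correlation ρ between baseline and follow-up LARS of 0.2 to 0.7.

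**Step 1: the plan's own figure.** With n per arm, the noncentrality is δ / (SD × √(2/n)) on 2n − 2 degrees of freedom. Since no SD is given, I solve for the one that yields 80% at n = 17:

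- SD = 5.045 gives 5 / (5.045 × √(2/17)) = 5 / (5.045 × 0.343) = 2.889. On 32 df (critical value 2.037) the power is 80.0%.
- With SD 5.0, 17 per arm gives 80.7% and 16 gives 78.1%, so 17 is the smallest adequate number.
- The normal approximation implies SD 5.20. A one-sided 0.05 test would imply 5.74 (exact t) or 5.86 (normal approximation).

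So 17 per arm is reproducible only with an assumed SD and alpha. The figures below use 5.045 and two-sided 0.05.

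**Step 2: variance of the three candidate analyses**, relative to the raw-score t test:

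- ANCOVA on baseline: 1 − ρ², with one degree of freedom less (31).
- t test on change, equal variances at baseline and follow-up: 2(1 − ρ).
- ANCOVA against change: (1 − ρ²) / [2(1 − ρ)] = (1 + ρ)/2, which is below 1 for every ρ below 1.

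If the variances differ, with k the ratio of baseline SD to follow-up SD, the change-score factor is 1 + k² − 2kρ. Its excess over ANCOVA is (1 + k² − 2kρ) − (1 − ρ²) = (k − ρ)², never negative. So ANCOVA has no larger residual variance under either reading, but the size of the change-score penalty depends on k.

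**Step 3: power at 17 per arm** (raw-score t test 80.0%):

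| ρ (assumed) | ANCOVA factor | ANCOVA power | Change factor (k = 1) | Power, t test on change |
|---|---|---|---|---|
| 0.2 | 0.96 | 81.5% | 1.60 | 60.1% |
| 0.3 | 0.91 | 83.5% | 1.40 | 65.8% |
| 0.5 | 0.75 | 89.8% | 1.00 | 80.0% |
| 0.7 | 0.51 | 97.5% | 0.60 | 95.1% |

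Worked line for ρ = 0.3. ANCOVA: residual SD 5.045 × √0.91 = 4.813, noncentrality 3.029, power 83.5%. Change: SD 5.045 × √1.4 = 5.970, noncentrality 2.442, power 65.8%.

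If the baseline predicted nothing (ρ = 0), ANCOVA would have 79.9%. The lost degree of freedom therefore costs about 0.1 percentage point.

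**Step 4: if the planned 20% is lost.** 20 × 0.8 = 16 per arm remain. The raw-score t test then has 77.4%, and ANCOVA 79.0%, 81.1%, 84.0% and 87.9% at ρ = 0.2, 0.3, 0.4 and 0.5.

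These gains are for ANCOVA at a single visit. With complete data, a mixed model's contrast at one visit has similar precision. Its further benefit comes when some scores are missing.

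**The case against.** Several points on the other side have force.

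- **The t test is valid.** Under randomisation an unadjusted comparison is unbiased, and its standard error already allows for chance imbalance at baseline. This stands: the loss is precision only.
- **The gain may be small.** Admitting only patients above 30 narrows the baseline range and may lower ρ; at 0.2 the gain is 1.5 points of power. This also stands, but the price is close to nothing.
- **The test may be on change.** The Objectives and Outcome measures sections make that plausible, so it cannot be said flatly that baseline is ignored. Nor is a change score always harmful: at ρ = 0.5 it equals the raw score, and at 0.7 it is far better. ANCOVA is still ahead in each case.
- **A mixed model costs more than one degree of freedom.** An unstructured covariance over four visits has 4 × 5 / 2 = 10 parameters, with at most about 20 patients per arm. This is a fair reason to specify a small-sample correction, or to prefer ANCOVA.

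A reader might infer something stronger: that the t test discards every patient without a score and so breaks the intention-to-treat promise, especially as the Introduction reports of an earlier trial that "six patients, reduction of 27.27%) dropped out of the intervention (TAI) group". The article does not support this. It states no rule limiting the analysis to completers, and the 20% is a recruitment allowance. Questionnaires are not limited to patients who continue irrigation. Analysing patients as randomised is compatible with a t test. Missing-data handling, including imputation, may sit in an analysis plan that is not shown. It would also be too much to say that three of the four visits are ignored, since no primary visit is named.

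**Conclusion.** The point holds as one of efficiency. The named primary test is a weak choice for a design with a baseline score on every patient and four scheduled follow-up scores, and a baseline-adjusted comparison is preferable whether the raw score or the change was meant.

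Against the raw-score test at 17 per arm, the gain is 1.5 points of power at ρ = 0.2, 3.5 at 0.3, 9.8 at 0.5 and 17.5 at 0.7. Against the change-score test it is 21.4, 17.7, 9.8 and 2.4 points. These figures rest on two-sided alpha 0.05, an SD back-solved from the plan's own sample size and an assumed range for ρ. The change-score figures also assume equal variances at baseline and follow-up, which the entry threshold may upset. The article supplies none of these quantities, so the direction is firm but the size is not. There is no finding of bias, and none that the plan excludes patients or departs from intention to treat.

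**What to change.** In the Sample size and Statistical analysis sections, replace the unpaired t test with a baseline-adjusted comparison of LARS at one named visit, for example 12 months. Either form would do:

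- **ANCOVA:** LARS at that visit on arm and baseline LARS.
- **Mixed model for repeated measures:** LARS at 3, 6, 9 and 12 months on baseline LARS, arm, visit and arm-by-visit, with a stated covariance structure and a small-sample degrees-of-freedom correction (Kenward–Roger or Satterthwaite). The primary result is the arm contrast at the named visit.

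Report the difference with its 95% confidence interval, by randomised arm. If some scores are missing, the mixed model keeps every patient with at least one follow-up score, which fits the intention-to-treat statement better than a t test at a single visit.

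The cost is one degree of freedom for ANCOVA, plus the covariance parameters for the mixed model. Both can be run in SPSS, the package the article names, and neither needs a new visit or questionnaire. The Trial status section reports 24 patients included by January 2024, so the change should be dated and recorded before outcomes are examined by arm.

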### Outcome measures

The objectives of the trial are to evaluate in what proportion of patients (percentage) transanal irrigation and in what proportion of patients (percentage) the best supportive treatment reduces the symptoms of LARS score (change in absolute score), compare the results, and evaluate the statistical reliability. The secondary outcomes would be assessing the change in single LARS score's items.

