## Objectives

The primary objective of this study was to evaluate if transanal irrigation improves bowel function and quality of life in patients following low anterior resection compared with best supportive care.

Specific objectives were as follows:
1.To assess the proportion of patients with transanal irrigation that reduces the symptoms of LARS (decrease in absolute score).2.To assess the proportion of patients with best supportive care that reduces the symptoms of LARS (decrease in absolute score).3.Compare results between groups.

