## Methods and analysis

### Study design

This is a multicenter randomized clinical trial. Centers from Lithuania (four centers), UK (at least one center), Denmark (at least one center), and other countries will be invited to participate through the European Society of Coloproctology’s (ESCP) trial map.

The main objective of this clinical trial is to evaluate whether transanal irrigation improves bowel function and quality of life in patients following low anterior resection best supportive care. This will be accomplished by recording the patient's complaints (defecation, urination problems, deterioration of quality of life) after the operation, filling the LARS score (3, 15), Wexner score (16), and quality of life questionnaires [European Organization for Research and Treatment of Cancer (EORTC) CR29 (17) and Measure Yourself Medical Outcomes Profile (MYMOP)] (18) with additional questions: Would you advice this treatment to anybody else? Did your quality of live improve? Did the bowel function improve? Are you satisfied with the treatment? Did you expect the treatment would help? These questions will be rated from 0 to 5. All will be filled in again during the visit every 3 months for 1 year.

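### The endpoint labelled primary (LARS score by unpaired t test) does not match the outcome and objective sections (proportion of patients whose score falls), and no visit is named for the primary comparison

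*Protocol article*

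**What the plan says.** **Sample size section.** This is the only place where a variable is called primary: "The primary endpoint was LARS score analyzed by unpaired" *t* test. The calculation is for a difference in score points: "To demonstrate a 5-point difference (with 80% certainty) between the intervention group and the control group, 34 patients were required", that is 17 per arm. It continues: "Taking into account a drop off of 20%, at least 20 patients per group will be needed".

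**Outcome measures section.** The quantity to be evaluated and compared is a percentage of patients, given for irrigation and again for the control arm: "in what proportion of patients (percentage) the best supportive treatment reduces the symptoms of LARS score (change in absolute score"). The next sentence is "The secondary outcomes would be assessing the change in single LARS score's items". The total LARS score as a continuous outcome does not appear in this section, either as main or as secondary outcome.

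**Objectives section.** The first specific objective is "To assess the proportion of patients with transanal irrigation that reduces the symptoms of LARS (decrease in absolute score"). The second says the same for best supportive care, and the third compares the two groups.

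**Timing.** Study design has "All will be filled in again during the visit every 3 months for 1 year", and Assessments has "Questionnaires and scales will be filled again during the visit every 3 months for 1 year". That gives four post-baseline visits, at 3, 6, 9 and 12 months. No section says which one carries the primary comparison.

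The Data analysis and Statistical analysis sections add only the software and the intention-to-treat principle.

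**The concern.** An analyst who follows the Sample size section compares two mean scores. One who follows Outcome measures and Objectives compares two percentages. These are different estimands with different tests, and they can disagree. Many small falls in one arm move the percentage and hardly move the mean; a few large falls do the opposite.

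Two further choices are open. The visit is not named. The metric is also unclear, because the t test is tied to the score while the other sections speak of a change or a decrease in absolute score. For the proportion, no threshold is fixed: any fall might count, or only a fall of the 5 points named in the sample size.

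The primary variable and its time point are what a sample size is calculated for. Two printed versions that differ are a contradiction within the article, not a detail left to another document. What is at stake is the nominal 5% error rate and whether the 80% power applies to the result that will be reported as the main one.

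**Working it through.** **Inputs from the article:** 5-point difference, 80% power, 17 evaluable per arm, equal allocation, four post-baseline visits.

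**Assumptions, because the article gives no figure:** two-sided alpha 0.05; SD of the LARS score; correlation between visits; correlation between baseline and follow-up; mean change in controls; Fisher's test for the proportion.

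**1. Reproducing 17 per arm.** The normal approximation is n = 2(1.96 + 0.84)² × SD² / 5². With SD 5.05 this is 15.7 × 25.5 / 25 = 16.01, rounded up to 17. SDs from 5.05 to 5.20 give 17 by this formula, and SDs from 4.89 to 5.04 give 17 by exact t-test power. The stated size is therefore attainable for a two-sided t test if the SD is about 5, but that SD is back-solved from the answer. At 17 per arm, t-test power for 5 points is 80% at SD 5.05, 65% at SD 6 and 42% at SD 8. Nothing in this calculation concerns a proportion.

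**2. Free choice of visit.** Null trials were simulated (20,000 or more per setting, 17 per arm, four equally correlated visits, each test at 0.05). If the four tests were independent, the rate would be 1 − 0.95⁴ = 18.5%. With correlation:

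| Between-visit correlation | t test, one fixed visit | t test, any of 4 visits | t test or Fisher on any decrease, any of 4 visits |
|---|---|---|---|
| 0.5 | 5% | 15–16% | 18–19% |
| 0.7 | 5% | 13% | 16% |
| 0.9 | 5% | 9–10% | 12% |

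Fixing one analysis at one visit restores 5%.

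**3. Power for the proportion.** Let the score SD be 5.05 and the baseline–follow-up correlation r. The SD of the change is 5.05 × √(2(1 − r)). With whole-point scoring assumed, a patient counts as improved if the modelled fall exceeds 0.5, so P(improved) = Φ((mean fall − 0.5) / SD of change). The irrigation arm falls 5 points more than control. Exact Fisher power at 17 per arm:

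| r | SD of change | Controls unchanged | Controls improve 5 points |
|---|---|---|---|
| 0.3 | 5.98 | 0.47 v 0.77: 33% | 0.77 v 0.94: 15% |
| 0.5 | 5.05 | 0.46 v 0.81: 45% | 0.81 v 0.97: 13% |
| 0.9 | 2.26 | 0.41 v 0.98: 97% | 0.98 v 1.00: near 0% |

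Counting any modelled fall above zero instead, with change SD 5, gives 43% and 8%, close to the middle row. The same true 5-point effect can thus leave the proportion well powered or hopeless, depending on quantities that the article does not state.

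**4. Score or change.** At r = 0.3 the SD of the change is 5.98, so a t test on the change has about 65% power (the SD 6 figure in step 1) against 80% on the score. The unstated metric matters as well.

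**The case against.** Only one version carries the word primary. Outcome measures speaks of the objectives of the trial, and Objectives places the proportions among specific objectives, beneath a broader primary one. A reader might infer that the plan declares two rival primary endpoints, so that eight analyses have equal standing. The text does not support that: the proportion is primary only by position, because the secondary outcomes follow it. The mismatch remains, since the outcome section leaves out the endpoint on which the trial was sized.

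The article is condensed, and a full protocol, an analysis plan or the registry entry may name the visit. The gap is therefore shown for this article only. The disagreement between its own sections is unaffected.

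The error rates describe picking the best of several results, which no section proposes. A reader might also infer that results have already been seen, since 24 of the planned 40 patients were enrolled by January 2024. Enrolment began in August 2023, and nothing reports a comparative look. Data analysts receive only group letters. That protection is weak, because the Randomization section says which letter is irrigation, but it should be acknowledged.

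The abstract calls the trial hypothesis-generating, which lowers the stakes of a type I error. Even so, the trial has a powered primary test, and that test should be identifiable.

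Finally, it is tempting to say that the proportion version is underpowered. The range in step 3 does not allow that as a general statement.

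**Conclusion.** The point holds as an internal mismatch with real consequences. The labelled and powered primary endpoint is absent from the outcome section, the proportion stands in its place there and in the objectives, and the article fixes neither the visit nor the choice between score and change. Following the plan as written allows different primary tests.

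If that freedom were used, the false-positive rate would be about 15–16% to 10% for a choice among four t tests, and about 18–19% to 12% with Fisher's test added. These figures assume two-sided alpha 0.05, 17 per arm and between-visit correlation 0.5 to 0.9. They measure available flexibility, not a planned procedure or an accusation.

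The stated 80% power belongs to the continuous version only. For the proportion, power runs from about 33% to 97% if controls do not change and from about 15% to near 0% if they improve by 5 points (score SD 5.05, baseline–follow-up correlation 0.3 to 0.9), so no single figure can be defended.

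**What to change.** Align Objectives and Outcome measures with Sample size. State one primary endpoint: the between-arm difference in mean LARS score at one named visit. Twelve months, the end of scheduled follow-up, is a natural choice, but the sponsor may justify another.

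State the metric. Adjustment for the baseline LARS score, which is already collected, is preferable and settles the question of score or change. It replaces the plain unpaired t test, so it is a recommendation and not a condition for resolving the mismatch.

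Make the other three visits and the proportion of improvers secondary, with the threshold for improvement stated. Date the amendment before any comparative look at the data, and check that the registry entry agrees.

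The cost is a wording amendment and the loss of the proportion as a headline result. No extra patients or visits are needed.

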### Data analysis

Statistical methods will be used for data analysis using the SPSS program.

### Statistical analysis

For statistical analysis, we will use the intention to treat principle.

## Data collection and management

### Data collection

Data obtained from demographic and clinical examination during the initial assessment and from the medical documentation at the study center will be collected. List of data to be obtained are subject's gender, age, height, weight, concomitant diseases, and medications used (their names and doses). The patient's complaints (defecation, urination problems, deterioration of quality of life) after surgery are recorded; LARS is evaluated according to questionnaires at each visit. The data collected via paper will later be uploaded into Excel, where it will be depersonalized. All questionnaires used have been validated (Wexner, LARS), or permission to use them has been obtained from the authors.

